**5.3 Data source and Population**

*Study population and size*

The Site 1 feasibility study will be a pilot study involving n=15 (n=20 with 33% dropout) participants per group. This study will evaluate the capability of the experimental device to provide instrumented BF (create distinct BF exercise profiles and is understood by the user) and compare the data against anorectal manometry. This is similar to our previous study [18] but will use the new prototype (V2) and be in a patient population.

The data from this site will not be analysed together with data from Site 2, given the differences in methodology. However, data from Site 1 will be used to improve the statistical analysis plan for Site 2. Currently, the power calculations for Site 2 are based on a previous study [19], but data from Site 1 will be integrated to improve the calculation of sample size and power for Site 2.

Site 2 sample size and power calculations

Based on a previous study of biofeedback treatment for faecal incontinence [19], we estimate that for assessing home-BF and clinic-BF efficacy with a sample size of 30 per group (n=40 with 33% dropout), the paired t-test at the 0.05 significance level can detect a mean change in anorectal function measure of at least 0.45 SD with 0.80 power. This corresponds to at least a mean decrease of 8 in Vaizey/Wexner faecal incontinence score, decrease of 0.6 in faecal incontinence episodes, and 40% increase in anal sphincter squeeze pressure.

For the non-inferiority study, based on changes in the primary outcome measures, with n=30 per study arm, the test for non-inferiority has 0.70 power to reject, at the 0.05 significance level, the null hypothesis that the mean change due to home-BF is smaller than clinic-BF by at least 0.44 SD in favour of he alternative hypothesis that mean changes due to home-BF is no more than 0.44 SD lower than clinic-BF (i.e. Ho: ΔHB-ΔOB<−0.44SD vs. Ha: ΔHB-ΔOB≤−0.44SD).

Using estimates from previous study [19], we consider home-BF no worse than or better than clinic-BF if the home-BF group had at least 9 point decrease in Vaizey/Wexner faecal incontinence score (11 for clinic-BF, SD=3), 0.95 days/week decrease in faecal incontinence episodes (1.1 for clinic-BF, SD=0.25), and 19 mmHg increase in anal sphincter squeeze pressure (25 mmHg for clinic-BF, SD=10).

*Data collection/Outcome measurements*

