**During biofeedback therapy**

- Participants keep a physical or digital bowel diary (bowel habits, stool consistency, symptoms)
- Participants keep a physical or digital food diary (meals, macro nutrients consumes, fibre consumed)
- The Vaizey and Wexner faecal incontinence score completed at the first and last appointment [20, 21]
- A the last appointment, participant provide self-evaluation of treatment efficacy and change [22]

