**5.8 Study Procedure**

Patients arrive at a study site to undergo routine diagnostic anorectal manometry. If a patient is diagnosed with a functional faecal incontinence and suitable for BF therapy they will be asked to take part in this study. Randomization used permuted blocks of 4 with 1:1 assignment into the parallel study groups described in Section 5.3. Random numbers generated in advance and placed into sequentially numbered opaque envelopes, sealed and used for subject assignment. After screening, and once patients met the study inclusion and exclusion criteria, patients are enrolled into one of the treatment arms, by opening the sealed envelope. The therapist ([name] or [name]) and patient are not blinded to the treatment.

The specialist nurse therapist provides advice regarding bowel habits, exercise, laxatives, dietary fibre and fluid intake, and timed-toilet training during the initial consultation to all participants. The therapist will teach participants how to improve their push effort by using postural and diaphragmatic breathing techniques and instruct them to practice these manoeuvres at home for 15 minutes, three times a day.

*Clinic-based biofeedback using anorectal manometry*

In addition to the aforementioned general instructions, participants receiving clinic-based BF (**Group A**) will be attending a maximum of six in-clinic therapy sessions over 2 months. BF training uses the anorectal manometry. Manometry catheters have several circumferential pressure sensors that straddle the entire anal canal and a proximal sensor placed in the rectum, providing continuous and dynamic spatiotemporal mapping of anorectal pressures. During anorectal BF therapy, a sheath is placed over the catheter and inserted into the anal canal. The system and therapist provides provide visual/audio feedback to the patient and record exercise parameters to establish baseline or evaluate progress. The key BF manoeuvres are:

1. **Rest:** after probe placement, a period of time is given for the patient to relax such that anal sphincter tone returns to basal levels. Anal resting pressure is measured using the averaged resting pressure over the length of the anal canal over a period of 20 seconds. This pressure is a composition of the internal and external anal sphincter and, to a lesser extent, by the hemorrhoidal plexus.

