2. **Squeeze and hold:** The patient is asked to squeeze the anus for as long as possible, for a maximum of 30 seconds. By convention, this manoeuvre is performed three times. Both the maximal contractile pressure and endurance times are measured. Ideally, rectal pressure should not increase, because that would imply the patient has contracted the abdominal wall.
3. **Simulated defecation (push):** The patient bear down as if to defecation and attempt to expel the catheter. This manoeuvre should produce sufficient rectal propulsion pressures with simultaneous anal sphincter relaxation (>20% relaxation).

During treatment period, patients are asked to keep a bowel and food diary. During their in-clinic visits, the therapist will provide consultation on the patient’s progress and any changes to clinical indicators.

*Home-based biofeedback using new device*

In addition to the general instructions, patients selected for home-based BF with novel device (**Group B**) will be trained on the use of home-training device by the therapist. For feasibility study at Site 1, participants will use the device in the clinic under supervision for a maximum of six sessions.

Accuracy and repeatability of prototype V2 will be assessed in the first five (n=5) group B participants. Participant manometry parameters (e.g. resting, push, squeeze) will be compared against the prototype data during their first training session. Capabilities of the V2 sensors will compared against previous V1 data [18] to determine if the V2 prototype is suitable for use. If V2 sensors are not deemed suitable, the trial will be temporary suspended while the technical issues are resolved. During this time, the participant will be removed from the study and begin conventional treatment. If V2 sensors are suitable the participant will continue with trial and subsequent sessions.

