**Site 1 and 2 analysis**

The manometric parameters (maximum anal sphincter squeeze pressure (mmHg) and mean anal sphincter resting pressure (mmHg)) for the period before treatment would be compared against parameters after treatment. Clinical indicators Vaizey/Wexner faecal incontinence score, faecal incontinence episodes (days/week), frequency of bowel motions & symptoms, and patient’s own view of effectiveness rating will be analysed. Univariate analysis (paired t-test or Wilcoxon) will be used to evaluate manometric parameter changes, while chi square test will be used to compare clinical indicators.

Non-inferiority study analysis described in Section 5.3 will be used to determine if null hypothesis is accepted or rejected.

***
[figure not shown]
***

***Figure 3.*** *Summary of study procedure*

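### The Site 2 paired before-after tests cannot show efficacy of home-BF or clinic-BF, because general advice starts in the same interval; conclusions should rest on the between-arm difference only

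*Protocol*

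**What the plan says.** Section 5.3 of the protocol sets two tests for Site 2.

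- **Within-arm test.** It is planned "for assessing home-BF and clinic-BF efficacy with a sample size of 30 per group (n=40 with 33% dropout), the paired t-test" at the 0.05 level, with 0.80 power for a change of 0.45 SD. It is sized on clinical outcomes as well as on squeeze pressure: "This corresponds to at least a mean decrease of 8 in Vaizey/Wexner faecal incontinence score, decrease of 0.6 in faecal incontinence episodes".
- **Between-arm test.** This is a non-inferiority test of home-BF against clinic-BF with a margin of 0.44 SD. A closing rule follows, under which home-BF counts as no worse than or better than clinic-BF "if the home-BF group had at least 9 point decrease in Vaizey/Wexner faecal incontinence score", with matching figures of 0.95 days/week and 19 mmHg. The clinic-BF expectations (11 points, 1.1 days/week, 25 mmHg) and the SDs (3, 0.25, 10) stand in brackets.

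Section 5.8 describes care common to both arms. The therapist "provides advice regarding bowel habits, exercise, laxatives, dietary fibre and fluid intake, and timed-toilet training during the initial consultation to all participants", teaches push, posture and breathing techniques, and is to "instruct them to practice these manoeuvres at home for 15 minutes, three times a day". Biofeedback in either arm comes on top of this.

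On timing, Section 5.3 (During biofeedback therapy) has "The Vaizey and Wexner faecal incontinence score completed at the first and last appointment". Section 5.8 adds, for the clinic arm, "During treatment period, patients are asked to keep a bowel and food diary"; the home arm keeps its diaries on the app. In Section 5.8 (Site 1 and 2 analysis), manometric parameters "for the period before treatment would be compared against parameters after treatment" by paired t-test or Wilcoxon, and clinical indicators are compared by chi-square.

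**The concern.** A paired test compares an arm only with itself before treatment. Between the two measurements each participant starts biofeedback, and also advice on laxatives, fibre, fluids, exercise and timed toileting plus 15 × 3 = 45 minutes a day of taught practice. For comparison, the home device is used for 5 to 10 minutes a day. No period is stated in which the advice could take effect before the baseline score, and no arm gets the advice without biofeedback. Natural course and regression to the mean act in the same interval.

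A significant paired result therefore says that patients changed. It does not say that biofeedback, by either route, changed them. Randomisation does not help, because this test ignores the other arm. Non-inferiority does not supply the missing step either: it can show home-BF no worse than clinic-BF, but not that either adds to the advice.

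The closing rule has a related weakness. Read literally, it asks only how far the home arm fell, so change from any source counts towards it, and the clinic arm's observed result does not enter.

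**Working it through.** **1. The plan's own figure.** Inputs from Section 5.3: n = 30, change 0.45 SD, alpha 0.05 (sidedness not stated), power 0.80. For a single-group test on change scores, the normal approximation gives power = Φ(0.45 × √30 − z).

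- One-sided, n = 30: Φ(2.465 − 1.645) = 0.794 (noncentral t: 0.777)
- Two-sided, n = 30: 0.693 (noncentral t: 0.664)
- Two-sided, n = 40: 0.812 (noncentral t: 0.793)

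The stated 0.80 is reproduced as a one-group before-after test, one-sided at 30 or two-sided at 40. No control arm enters it.

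**2. The paired test when biofeedback adds nothing.** Assumption: general care alone moves the outcome by d SD of change. The documents give no value for d, so a range is shown. With SD 3, 0.2 to 0.6 SD is 0.6 to 1.8 score points. P(significant for benefit) = P(noncentral t with 29 df and noncentrality d × √30 exceeds the critical t).

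| d (SD) | two-sided 0.05 | one-sided 0.05 |
|---|---|---|
| 0 | 0.025 | 0.050 |
| 0.2 | 0.184 | 0.283 |
| 0.3 | 0.355 | 0.484 |
| 0.45 | 0.664 | 0.777 |
| 0.6 | 0.888 | 0.941 |

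**3. The between-arm test.** An additive advice effect that is equal in both arms cancels in the difference. In 100,000 simulated trials (30 per arm, margin 0.44 SD, one-sided 0.05, arms truly equal), non-inferiority was declared in 0.51 to 0.52 of trials, whether the shared advice effect was 0 or 0.6 SD.

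**4. The closing rule read literally.** SE of the home arm's mean = 3/√30 = 0.548 points. P(observed mean decrease ≥ 9) is 0.034 if the true total decrease is 8, 0.500 if it is 9, and 0.966 if it is 10. One or two points from any source decide the result. The true totals are illustrative.

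**5. The rule turned into between-arm differences.**

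| Outcome | Difference implied by the rule | In SD | 0.44 SD in units |
|---|---|---|---|
| Score | 11 − 9 = 2 points | 2/3 = 0.67 | 0.44 × 3 = 1.3 points |
| Episodes | 1.1 − 0.95 = 0.15 days/week | 0.15/0.25 = 0.60 | 0.44 × 0.25 = 0.11 days/week |
| Squeeze pressure | 25 − 19 = 6 mmHg | 6/10 = 0.60 | 0.44 × 10 = 4.4 mmHg |

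The rule and the formal hypothesis therefore carry different margins.

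**The case against.** The trial's hypothesis is that home-BF is as efficacious as clinic-BF, and Section 5.8 leaves acceptance or rejection of the null hypothesis to the non-inferiority analysis. That stands, and the main comparison is sound on this point.

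Section 5.8 names the paired test only for manometry, where advice on laxatives and fibre should matter little. This also stands in part: for scores and episodes the paired test rests on Section 5.3 alone. But Section 5.3 sizes it on those outcomes explicitly and calls the purpose efficacy.

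Home-BF can be read as the whole package, advice included. That narrows the attribution problem but does not remove it, since natural course and regression to the mean are still in the within-arm change.

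The closing rule follows the non-inferiority hypothesis and quotes the clinic-BF figures, so a between-arm margin is probably meant. Even so, the words set a threshold for the home arm alone, and the margin they imply is not 0.44 SD.

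A reader might infer more: that the paired test will carry a stand-alone device claim to the regulator. Section 7.1 says that the study's data will form part of a submission, but no section says that this test will support such a claim. A reader might also infer that co-interventions go unrecorded. The food diary includes fibre, and the case report forms are not shown.

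**Conclusion.** The point holds in a limited form. The paired tests in Section 5.3 cannot show efficacy of home-BF or of clinic-BF, and the closing rule should not be decided by the home arm's own change. The randomised non-inferiority test is untouched, provided the advice acts equally and additively in the two arms.

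The size depends on an assumption. For a non-biofeedback change of 0.2 to 0.45 SD and no biofeedback effect, the paired test signals benefit in 18% to 66% of trials two-sided, or 28% to 78% one-sided. These are points on a power curve for an assumed shift, not evidence that such a shift will occur. It is tempting to take the stated power and say that an advice effect of 0.45 SD would be declared efficacy in 80% of trials. With 30 participants and the t-test, the figure is 66% two-sided or 78% one-sided. The concern is greatest for scores and incontinence episodes and small for squeeze pressure.

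**What to change.** 1. In Sections 5.3 and 5.8, stop calling the paired analysis an assessment of efficacy. Report each arm's mean change with a 95% CI as descriptive change under biofeedback plus general advice, and draw conclusions only from the between-arm difference in change.

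2. Reword the closing rule: home-BF is non-inferior on an outcome if the confidence bound for the difference in mean improvement (home minus clinic) lies above minus the margin. State the sidedness and choose one margin: either 0.44 SD (1.3 points, 0.11 days/week, 4.4 mmHg) or the differences implied by the present rule (2 points, 0.15 days/week, 6 mmHg). The choice should be justified clinically. It also matters for power: with 30 per arm, truly equal arms and one-sided 0.05, the normal approximation gives about 0.52 at 0.44 SD, 0.75 at 0.60 SD and 0.83 at 0.67 SD.

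Both are wording changes and add no visits or participants. The cost is that the paired test no longer yields a stand-alone efficacy claim. No advice run-in is required: it would delay therapy and would serve a within-arm claim that the trial's hypothesis does not make.

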**3. AIMS/OBJECTIVES/HYPOTHESES**

*Aim*

To compare the treatment efficacy of anorectal biofeedback (clinical indicators and physiological parameters) performed with a novel home-based device with conventional therapy options in patients with functional defecation disorders.

*Faecal incontinence is a heterogeneous condition, there is no single parameter to adequately define or represent an optimal way of assessing clinical outcomes. A range of subjective and physiological measures of bowel function are used as outcomes measures.*

*Site 1 Specific* - A feasibility assessment at Site 1 will evaluate the accuracy and repeatability of the prototype (V2) against anorectal manometry*

1. *Evaluate the capability of experimental device to generate anorectal exercise profiles*
2. *Compare the accuracy of experimental device against anorectal manometry*

*Site 1 and Site 2*

*Subjective primary outcome measures*

1. *Vaizey and Wexner faecal incontinence scores*
2. *Faecal incontinent episodes (days per week)*

*Objective primary outcome measure*

1. *Anal sphincter squeeze pressure (mmHg)*

*Secondary outcome measures*

1. *Anal sphincter resting pressure (mmHg)*
2. *Patient’s own view of effectiveness rating (“worse”, “same”, “improved”, or “cured”) and rating of that change in an ordinal scale of – 5 to + 5*
3. *Frequency of bowel motions and symptoms*
4. *[Experimental device group] Usability interview – 1. Ease of use, 2. Clarity of instructions, 3. Ease of cleaning, 4. Any additional Issues*

Hypotheses

We hypothesised that instrumented home BF therapy with the novel device is as efficacious as clinic-based BF therapy

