Group B participants will undergo 6 supervised clinic sessions with the experimental device. After session two, they may also take the device home and continue training during the treatment period. The wireless device contains sensors to measure anal sphincter and rectal pressures. A condom sheath is placed over the probe before it is inserted into the anal canal. The user will download the training program (mobile app) onto their mobile phones, which will guide the user through the required exercises (identical to the clinic-based BF manoeuvres listed above). Participants will be asked to insert the probe and perform training for 5 – 10 minutes daily over a training period of 2 months. Training data is send to a cloud server for therapist to monitor compliance and correct usage. The participants are asked to keep daily bowel and food diaries on the app, this information is sent to the cloud accessible only by the therapist and investigators.

Upon completion of the feasibility study, home-based BF with novel device at Site 2 (Group B) will only undergo one supervised training session with the novel device. Participants then take the device home and continue training unsupervised for the duration of their treatment period. The therapist monitor adhesion remotely through the cloud server and will arrange fortnightly telehealth consultations to provide encouragement and evaluate progress.

At the end of the treatment period, participants in Group B will undergo a short useability interview. The therapist will ask the participant questions regarding the 1. Ease of use, 2. Clarity of instructions, 3. Ease of cleaning, 4. Any additional Issues.

*Data analyses*

At the end of the treatment period participants will return to the clinic for a repeat anorectal manometry study to determine changes in anorectal physiology parameters. The therapist will also review their bowel and food diaries. The therapist will discuss the results with the participants and plan the next course of action.

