The recording and reporting of adverse events will be classified based on their severity (“Negligible”, “Minor”, “Serious”, “Critical”, and “Catastrophic”). All events classified as “minor” or above in severity will be recorded and notified to the Principle investigator ([name]) and site coordinating investigator ([name]). Events classified as “Serious” or above will be will reported to HREA in to form of a “safety report” and trial will be temporarily suspended to investigate cause of event and implement appropriate mitigation strategies (e.g. instructions-of-use, technical updates, update cleaning procedure).

The clinicians involved in this study ([name] and [name]) will be available to help if any adverse events or symptoms occurs during the study. They will be able to provide medical advice and determine the best course of action.

To avoid coercion or inducement, an investigator not directly involved in the participant’s treatment (e.g. [name]) will be explaining the procedure and obtaining informed consent.

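### The usability interview is run by the therapist role that trained and monitored the participant, so answers may lean in the device's favour

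*Protocol*

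**What the plan says.** Protocol section 3 lists a usability interview as the fourth secondary outcome measure, for the experimental device group only. It names four topics and no response scale.

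Section 5.8 sets the time and the interviewer. On time: "At the end of the treatment period, participants in Group B will undergo a short useability interview". On the interviewer: "The therapist will ask the participant questions regarding the 1. Ease of use", followed by the other three topics.

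The same section says that Group B participants "will be trained on the use of home-training device by the therapist". It also has the therapist follow compliance and correct use through the cloud server, hold fortnightly telehealth consultations at Site 2, and discuss results and next steps with participants at the end of treatment. On blinding it states: "The therapist ([name] or [name]) and patient are not blinded to the treatment".

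Section 5.8 describes no self-completed questionnaire for usability and no interviewer from outside the treatment team.

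**The concern.** Participants are asked about the device, its instructions and its cleaning by someone in the role that taught them to use it, watched how they used it and will help decide what happens next. In that position some people soften criticism. If that happens, the answers will tend to favour the device.

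This is a listed outcome, and the protocol itself chooses how it is collected, so it is not a detail that could be waiting in an analysis plan. Candid answers have three uses:

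- Section 5.3 says the Site 1 study will look at whether users understand the biofeedback that the device provides. The clarity question asks users about something close to this.
- Site 1 participants have up to six supervised sessions and Site 2 device users have one, so problems with instructions matter more in the second phase.
- Section 7.1 says that study data will support a regulatory submission.

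**Working it through.** No calculation applies to the bias itself. The check sets the relevant statements side by side.

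**1. Is the interviewer the same role as the trainer?** Yes. Section 5.8 assigns device training, monitoring and the usability questions to the therapist. Two people are named for that role, one or the other. The interviewer is therefore certainly of the same role and probably, but not certainly, the same individual. Nothing requires the two to differ.

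**2. Is there a safeguard?** None is described for this outcome. For consent, section 7.2 does separate roles: "To avoid coercion or inducement, an investigator not directly involved" in treatment explains the procedure. Nothing comparable is stated for the interview.

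**3. Is the interview in person?** Not stated. Section 5.8 says "At the end of the treatment period participants will return to the clinic for a repeat anorectal manometry study", which makes an in-person interview plausible, but the interview is not tied to that visit and Site 2 also uses telehealth. The concern rests on the interviewer's role and holds for either mode.

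**4. Whose instructions are being judged?** More than one source. The therapist trains the participant, the app guides the exercises (section 5.8), and the labelling carries directions for use (section 7.2, Table 2). The clarity question may concern any of these.

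**5. How many participants?** Section 1 plans 20 device users at Site 1 and 40 at Site 2: 20 + 40 = 60 at most. Section 5.3 sizes the groups for 15 and 30 after dropout, so about 15 + 30 = 45 end-of-treatment interviews if that assumption holds. Section 5.3 keeps the sites apart in analysis, so these are two separate sets of answers.

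**6. What does the outcome feed into?** The outcome exists in one arm only. The Site 1 and 2 analysis in section 5.8 includes it in no comparison, and the power and non-inferiority statements in section 5.3 do not use it. The V2 suitability decision in section 5.8 rests on sensor data, and no progression rule refers to the interview.

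**7. Can the size be computed?** No. The protocol gives no usability score, scale, threshold or expected value. The favourable direction is a reasoned expectation and not a derived result.

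**The case against.** The strongest case against is that the protocol states nothing false here and contradicts nothing. The outcome is secondary, descriptive and single-arm. In a pilot, a therapist who knows the prototype can probe in a way that a form cannot, and one of the four topics openly invites problems. Other evidence on use does not depend on what participants say: the cloud training data show compliance and correct use, and at Site 1 difficulties can be seen in supervised sessions. Harms have a separate reporting route in section 7.2.

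All of this stands, and it limits the weight of the point. It also rules out several stronger readings that a reader might infer:

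- *That scores are inflated.* There are no scores. Where the protocol wants a rating it says so, as with the −5 to +5 change scale in section 3. For usability it lists topics only.
- *That bias is established.* The text supports a risk of favourable answers and no more.
- *That this is the only evidence of user acceptance, or the feasibility evidence that opens Site 2.* It is the only participant-reported usability measure listed, but the training data also bear on use, and the Site 1 aims in section 3 concern exercise profiles and accuracy against manometry.
- *That contamination control depends on it.* Wiping the probe is one of three measures in Table 2, beside single-person labelling and the sheath.
- *That the protocol recognised response bias and then overlooked it.* The separation of roles in section 7.2 guards against pressure to consent, which is a different problem.

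The objection does not remove the core. A listed outcome is collected by the role that delivered the training, and the therapist's probing can be kept while the participant's own answer is recorded first.

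**Conclusion.** The point holds in a narrow form. The therapist role that trains and monitors device users also conducts the usability interview, and no self-completed or independent collection is described. Answers on ease of use, instructions and cleaning may therefore be favourably biased.

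The size is not computable from the protocol. The reach is at most 60 participants in one arm. No primary outcome, power figure or non-inferiority conclusion changes. The conclusion assumes that some participants hold back criticism in front of the role that treated them, which is reasonable but which the documents neither show nor exclude. It does not assume an in-person interview or that trainer and interviewer are the same individual. This is a cheap improvement, not a fault that threatens the trial.

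**What to change.** In section 5.8, where the interview is described, have Group B participants write their own answers to the four topics at the end of treatment, before the discussion with the therapist. Use a sealed paper form, or an in-app form that the therapist cannot see until it is submitted. The access condition matters because section 5.8 makes the app diaries available to the therapist and investigators, and an in-app form under the same access would not give the separation intended.

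Report these self-completed answers as the usability outcome, by site. Keep the therapist's interview afterwards as follow-up on any of the four topics, so that probing is not lost.

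Self-completion is preferable to simply naming another investigator as interviewer, because section 8 states that two investigators are inventors of the device.

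The cost is one short form for up to 60 device users, with no new visit and no change to sample size. The downside is that first answers will be less spontaneous. The change reduces the risk but does not remove it, since participants may expect the therapist to read the form later.
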